#### SUD treatment

Alongside PE, EMDR or ImRs, all study participants receive regular SUD treatment. Inpatient as well as outpatient participants can take part in the study. Standard care for SUD treatment includes both cognitive behavioral therapy (CBT) [46] as well as Acceptance and Commitment Therapy (ACT) [47]. Regular outpatient SUD treatment consists of 13 individual 50-min sessions (CBT or ACT) delivered by a psychologist (MSc) or cognitive behavioural therapist (BSc or MSc), supervised by a licensed healthcare psychologist. Regular inpatient SUD treatment consists of a 12-week CBT-based therapy program, of which the patient spends the first 6 weeks in the treatment facility receiving 24-h care. Patients in SUD day treatment follow a similar 12-week therapy program, for 3-days a week, 6-h a day. Timing and content of regular SUD treatment will not be modified due to or affected by participation in the study.

### Procedure

#### Recruitment

All patients attending an intake at the Jellinek Center are screened for PTSD with the J-PTSD screening questionnaire [30]. After the intake, the intramural or extramural SUD treatment is planned according to regular procedures and usually starts between 1 to 3 months after the intake. Patients with a positive PTSD screener are invited for further assessment with the Clinician Administered PTSD Scale for DSM 5 (CAPS-5) interview, also a regular procedure that is already implemented at the Jellinek Center. If the patient meets the criteria for PTSD, the psychologist informs the patient about the study and hands over the patient information letter. The psychologist asks consent of the patient for being contacted by telephone by a researcher to receive more information about the study. Potential participants receive written and oral information about the study and are invited for an informed consent procedure and screening of in- and exclusion criteria. Eligible patients are invited for the baseline (T0) assessment. Written informed consent is obtained prior to the assessment. All reasons of potential participants to decline participation in the study will be monitored.

#### Randomization and procedure

After the baseline assessment (T0), patients are randomly assigned to PE, EMDR, ImRs or SUD treatment only (each 25% chance). All patients receive SUD treatment shortly after the baseline assessment. Patients allocated to PE, EMDR or ImRs receive PTSD and SUD treatment simultaneously (75% of the sample), whereas patients in the 3-month SUD treatment only condition receive PTSD treatment after completing 3 months SUD treatment (25% of the sample). Patients in the SUD treatment only condition are randomly allocated to either PE (33% chance), EMDR (33% chance) or ImRs (33% chance) and start with the PTSD treatment after the 3 months follow-up assessment (T1).

After randomization, only disclosure of the timing will be given to the participants. Disclosure of treatment type will be done by the therapist at the start of the first session of the PTSD treatment.

Randomization is carried out by an independent researcher from Arkin who uses a computer-generated block randomization schedule. First patients are allocated to: simultaneous PE, simultaneous EMDR, simultaneous ImRs of sequential treatment with allocation probabilities per condition of 1/4. Block sizes are 4 and 8. Second, participants randomized to sequential treatment are allocated to: sequential PE, sequential EMDR or sequential ImRs, with allocation probabilities per condition of 1/3, after completion of the 3-months follow-up (T1) assessment. Block sizes are 3 and 6. Randomization is stratified by type of care (inpatient, daytreatment or outpatient) and location (Amsterdam or Utrecht). To prevent selection bias, all researchers are blind to order of block size and will not have access to the randomization schedule.

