### Sample size

First, we calculated the required sample size for the comparison between the three types of active PTSD treatments. Second, we calculated whether that sample size will provide sufficient power to compare the two timings of PTSD treatment. Three pairwise comparisons will be conducted between the active treatment arms (ImRs vs. PE, ImRs vs. EMDR; PE vs. EMDR). To detect a small-to-medium effect size (f = 0.15) in a pairwise comparison of pre-post change between two active treatment arms, with Bonferroni-corrected alpha = 0.0167, power = 0.85 and within-person correlation coefficient = 0.60, 54 participants are needed per arm. To make three pairwise comparisons 3 * 54 = 162 participants are needed. The allocation ratio between sequential and simultaneous PTSD treatment is 1:3. With *n* = 41 in sequential treatment and *n* = 121 in simultaneous treatment, power is 99% to detect a small-to-medium effect size (f = 0.15) in a comparison of pre-post change between simultaneous and sequential treatment, with alpha = 0.05, and within-person correlation coefficient = 0.60. To detect a small effect (f = 0.10) power is 81%. We expect 20% of the participants to drop out of the study, therefore in total 204 participants will be included in the study.

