##### Objective 1: comparison separate PTSD treatments with SUD treatment only condition at 3-month follow-up

The 3 treatment conditions will be compared with SUD treatment only condition (PE vs SUD; EMDR vs SUD; ImRs vs SUD) at 3-month follow-up (T1 measure) with a linear regression model. Baseline CAPS-5 score will be included as covariate.

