##### Objective 2: comparison timing of treatment, regardless of treatment type

The effect of timing of PTSD treatment on the primary outcome will be evaluated (simultaneous vs sequential) with (G)LMMs. Baseline CAPS-5 score will be included as covariate and timing of treatment as fixed effect. Overall effects will be evaluated, as well as between-group differences at separate follow-up time points (6-months and 9-months after baseline), by adding time and an interaction between group and time to the model. The intercept will be treated as a random effect.

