##### Objective 3: head-to-head comparison PTSD treatments, regardless of timing of treatment

The 3 treatment conditions will be compared head-to-head (PE vs EMDR; PE vs ImRs; EMDR vs ImRs) with (G)LMMs. Baseline CAPS-5 score will be included as covariate and treatment type as a fixed effect. Overall effects will be evaluated, as well as between-group differences at separate follow-up time points, by adding time and an interaction between group and time to the model. The intercept will be treated as a random effect.

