#### Secondary study parameters

Secondary outcome parameters will be analysed with (G)LMMs, with the underlying distribution depending on the type of outcome variable and its distribution, in accordance with the above described analyses.

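### Type of care and location stratify the randomisation but are absent from the stated outcome models; if they are prognostic, the linear models report standard errors modestly too wide

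*Protocol article*

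**What the plan says.** Under Randomization and procedure, the allocation uses two stratifiers: "Randomization is stratified by type of care (inpatient, daytreatment or outpatient) and location (Amsterdam or Utrecht"). That makes 3 × 2 = 6 strata. For the first randomisation, "Block sizes are 4 and 8".

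The Data analyses section then gives each primary model:

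- Objective 1 compares the conditions "at 3-month follow-up (T1 measure) with a linear regression model", and "Baseline CAPS-5 score will be included as covariate".
- Objective 2: "Baseline CAPS-5 score will be included as covariate and timing of treatment as fixed effect". Time, group by time and a random intercept follow.
- Objective 3: "Baseline CAPS-5 score will be included as covariate and treatment type as a fixed effect", with the same additions.

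Secondary outcomes are to be analysed with (generalised) linear mixed models "in accordance with the above described analyses". Neither type of care nor location appears anywhere under Data analyses.

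**The concern.** When patients are balanced on a prognostic factor by design, the treatment estimate no longer varies with chance imbalance in that factor. A linear model that omits the factor still counts its variance as residual noise, so it reports a standard error larger than the real spread of the estimate. Confidence intervals are then too wide, tests are conservative, and some power is lost.

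It is plausible that these factors carry prognostic information. The SUD treatment section describes very different background care: a 12-week inpatient programme with the first 6 weeks residential, a 12-week day programme of 3 days a week, or 13 individual outpatient sessions. The Methodological considerations section concedes that power may be too low for small differences between treatment types, so giving away precision is unhelpful.

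**Working it through.** **Step 1: the plan's own figures.** Inputs from Sample size: f = 0.15 ("To detect a small-to-medium effect size (f = 0.15) in a pairwise comparison of pre-post change between two active treatment arms"), alpha 0.0167, correlation 0.60, 54 per arm. For timing: 162 in total (41 and 121), alpha 0.05. A two-group, two-occasion repeated-measures F test has noncentrality λ = f² × N × 2 / (1 − 0.60).

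- N = 108, f = 0.15: λ = 0.0225 × 108 × 5 = 12.15, power 0.852 (stated 0.85).
- N = 162, f = 0.15: λ = 18.225, power 0.989 (stated 99%).
- N = 162, f = 0.10: λ = 8.1, power 0.808 (stated 81%).
- Dropout: 162 / 0.8 = 202.5, so 203; the plan has 204.

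The figures reproduce without any use of the stratification factors, so the sample size does not depend on this point.

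**Step 2: standard error and type I error, closed form.** Let R² be the share of outcome variance explained by the strata after baseline CAPS-5. The documents do not give it, so it is an assumption. With perfect balance, the unadjusted SE divided by the adjusted SE is 1/√(1 − R²), and the actual two-sided error at nominal 5% is 2 × Φ(−1.96/√(1 − R²)).

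| R² | SE ratio | Actual error |
|---|---|---|
| 0 | 1.00 | 0.050 |
| 0.02 | 1.01 | 0.048 |
| 0.05 | 1.03 | 0.044 |
| 0.10 | 1.05 | 0.039 |
| 0.20 | 1.12 | 0.028 |

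**Step 3: simulation of the actual design.** Perfect balance is optimistic with incomplete blocks in 6 strata and missing outcomes. The design was simulated with 204 randomised, blocks of 4 and 8, 20% missing, and a linear regression on condition and baseline. The case mix was assumed: 30/20/50% across the care types and 60/40% across the sites. There were 6,000 runs per value, so the Monte Carlo SE is about √(0.05 × 0.95/6000) = 0.003.

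| R² | Mean reported SE, factors omitted | True SD of that estimate | Type I error, omitted | Type I error, included |
|---|---|---|---|---|
| 0 | 0.178 | 0.178 | 0.052 | 0.051 |
| 0.05 | 0.178 | 0.174 | 0.043 | 0.048 |
| 0.10 | 0.178 | 0.171 | 0.043 | 0.051 |
| 0.20 | 0.178 | 0.164 | 0.032 | 0.049 |

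Further simulations of the same kind, with the factors omitted, gave about 0.049 to 0.050 at R² of 0.03 to 0.05, 0.038 to 0.039 at 0.10, and 0.030 at 0.20. At R² of 0.05 or less the departure from 5% is therefore hard to distinguish from simulation noise. At R² = 0.10 the true SD of the estimate is 0.171 without the factors and 0.169 with them. The estimate barely changes; what is lost is mainly reported precision.

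**Step 4: power, like for like.** Under stratification the true variance of the unadjusted estimate also falls with R². With s = √(1 − R²) and δ the difference divided by its SE at R² = 0, unadjusted power is Φ((δ − 1.96)/s) and adjusted power is Φ(δ/s − 1.96). For timing at f = 0.10, the difference in change is 4f = 0.40 and the SD of change is √(2 × 0.40) = 0.894. With 41 and 121, SE = 0.894 × √(1/41 + 1/121) = 0.1616 and δ = 0.40/0.1616 = 2.475.

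| R² | Omitted | Included | Gain (points) |
|---|---|---|---|
| 0.03 | 69.9% | 71.0% | 1.0 |
| 0.05 | 70.1% | 71.9% | 1.7 |
| 0.10 | 70.6% | 74.2% | 3.5 |

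These power levels treat f as the equal-group standardised difference. The stated 81% comes from a formula in total N, which is equivalent to 81 and 81. On that basis δ = 0.40/(0.894 × √(2/81)) = 2.846, and the gains are 0.8, 1.3 and 2.6 points. Which base is right is a separate question; the gain is similar either way.

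For a pairwise type comparison (54 per arm, alpha 0.0167), the same formulas with 2.394 in place of 1.96 give 86.5% against 87.0%, 86.9% against 88.1%, and 87.5% against 90.0% at R² of 0.02, 0.05 and 0.10.

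**The case against.** The strongest reply is that this is a condensed article. It says baseline CAPS-5 enters each model but never says that nothing else does. It also mentions prior distributions that it does not print, so a fuller specification exists and may contain the stratifiers. That possibility stands. Against it, the article names the covariate, fixed effects and random effect for each objective, and the models as stated do not match the randomisation. The point should be settled in the text.

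A second reply also stands: the size rests on an assumed R², the effect is small, and the error is on the safe side.

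Several stronger conclusions are tempting but unsupported:

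- A reader might infer that the tests are invalid or the estimates biased. They are not: stratified allocation balances the factors, and omission makes the linear analysis conservative.
- A reader might infer that adjustment lifts timing power from a fixed 69% to 74%. The 69% to 70% level is the R² = 0 value on one reading of f and differs from the stated 81%. It also ignores that unadjusted power rises with R².
- A reader might infer that omitting type of care undermines the handling of missing data. The article expects 20% dropout but links it to no type of care.
- A reader might carry the standard-error argument to the dichotomous outcomes. In logistic models, omission mainly attenuates the conditional effect.

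**Conclusion.** The mismatch between the stratified randomisation and the stated models is a textual fact. Its consequence is conditional and modest. If the strata predict CAPS-5 after baseline adjustment, the linear models report standard errors about 1% to 5% too wide for R² of 0.02 to 0.10; at R² = 0 there is no loss. Type I error is then at or below nominal: 4.8% down to 3.9% in closed form over that range, and close to 5% at R² of 0.05 or less in most simulations. The timing comparison at f = 0.10 loses about 1 to 3.5 points of power for R² of 0.03 to 0.10. The treatment contrast is not biased by the omission, and 54 per arm, 162 and 204 are unaffected. The case for acting is that the remedy is nearly free, not that the present analysis misleads.

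**What to change.** Add type of care (3 levels) and location (2 levels) as fixed effects to the Objective 1 regression and to the Objective 2 and 3 mixed models, and carry both into the secondary-outcome models. For outcomes with a non-linear link, such as loss of diagnosis, remission and treatment completion, state that adjustment changes the conditional effect being estimated rather than simply narrowing its standard error, and say which effect is to be reported. If the full analysis plan already contains these terms, one sentence saying so is enough.

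The cost is one line per model and 3 degrees of freedom (2 for care, 1 for location). Both factors are known for every patient at randomisation, so no new data are needed. Settle the choice before unblinding so that it cannot be driven by the results.

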#### Assessments

Assessments take place at baseline (T0), after 3 months (T1), 6 months (T2) and 9 months (T3). The T0 takes place within 1–2 weeks before the start of SUD treatment. Therefore, participants randomized to simultaneous SUD/PTSD treatment will receive PTSD treatment between baseline (T0) and 3-month follow-up (T1), whereas participants randomized to sequential SUD/PTSD treatment will receive PTSD treatment between 3-month (T1) and 6-month (T2) follow up. See also the flow chart in Fig. 1. All assessments are conducted by a junior researcher (MSc in Psychology), who is blind to treatment condition. In case of unblinding during an intermittent measurement, another assessor will administer the next measurement(s). All assessments consist of a 45–60 min interview-administered instrument to measure severity of PTSD symptoms (CAPS-5) and several self-report questionnaires. In total, assessments take 90–120 min to administer. All participants receive a gift voucher of €15 for each assessments to acknowledge the time and effort they provide in participating in the research. The self-report questionnaires that are administered are described in the following section and listed in Table 1.

**Table 1 Tab1:** Measurement instruments at every measurement moment

	Screening measurement	T0	T1	T2	T3
**Interview**					
CAPS-5		x	x	x	x
SCID-5-CV	x				x
**Self-report**					
BSI		x	x	x	x
AUDIT		x	x	x	x
DUDIT		x	x	x	x
MATE-Q module 1		x	x	x	x
DERS		x	x	x	x
IIP-32		x	x	x	x
TRGI		x	x	x	x
TRSI		x	x	x	x
ZECV		x	x	x	x
TiC-P			x	x	x
EQ-5D		x	x	x	x
Extension of LEC-5		x	x	x	x
ITQ (part 2)		x			
CTQ-sf		x			
DES subscale from SSQ		x			
STROOP & delay discounting task		x			x

Legend: *Abbreviations*: *CAPS-5* Clinician Administered PTSD Scale for DSM-5, *SCID-5-CV* Structured Clinical Diagnostic Interview for DSM-5 disorders – clinician version, *BSI* Brief Symptom Inventory, *AUDIT* Alcohol Use Disorder Identification Test, *DUDIT* Drug Use Disorders Identification Test, *MATE-Q module 1* Meten van Addicties voor Triage en Evaluatie, *DERS* Difficulties in Emotion Regulation Scale, *IIP-32* Inventory of Interpersonal Problems, *TRGI* Trauma-Related Guilt Inventory, *TRSI* Trauma-Related Shame Inventory, *ZECV* Zelf Expressie en Controle Vragenlijst, *TiC-P* Trimbos iMTA questionnaire for Costs associated with Psychiatric illness, *EQ-5D* EuroQol, *LEC-5* Life Events Checklist for DSM-5, *ITQ* International Trauma Questionnaire, *CTQ-sf* Childhood Trauma Questionnaire-short form, *DES* Daily Emotional Support subscale. Note T0–3 are subsequently the baseline assessment, and assessments at 3 month, 6 month and 9 month follow up

Furthermore, participants and their therapists also administer self-report questionnaires during therapy sessions. Study drop-out is minimized by having the follow-up assessments organized by the junior researcher, independently of the treatment facility, inviting participants for assessments regardless of treatment completion. Reminder calls are made before each assessment.

### Instruments

#### Eligibility screening

At the eligibility screening interview, SUDs are determined with the SUD criteria of the Dutch version of the Structured Clinical Interview for DSM-5 Disorders-Clinician version (SCID-5-CV) which is called the SCID-5-S [48]. Furthermore, in and exclusion criteria are assessed. A high suicide risk is checked with the suicide criteria of the Mini-International Neuropsychiatric Interview (MINI) [49] in combination with verifying if there was a suicide attempt in the last 3 months.

#### Primary outcome measure

The main study parameter is severity of PTSD symptoms and is measured at every assessment with the Dutch translation of the Clinician Administered PTSD Scale for DSM 5 (CAPS-5). The CAPS is the gold standard in PTSD assessment. It is a 30-item structured interview, corresponding to the DSM-5 diagnosis for PTSD, to assess PTSD symptoms over the past month. The sum of items 1 through 20 provides the total severity score [50]. The Dutch translation of the CAPS-5 has a high internal consistency for the full PTSD scale and a high interrater reliability score for the PTSD symptom severity score. Internal consistency for the symptom clusters is found to be acceptable [51]. All junior researchers were trained in the use of the CAPS-5 before conducting assessments and receive ongoing supervision throughout the study. Randomly selected CAPS-5 assessments are recorded on audio and scored by other researchers to check the interrater-reliability.

#### Secondary outcome measures

*Treatment completion:* Completion of PTSD treatment (yes/no) and completion of SUD treatment (yes/no) is administered by the involved therapists.

*Brief Symptom Inventory (BSI):* The BSI is a 53-item questionnaire that measures psychological distress and is developed from the longer Symptom Checklist (SCL-90-R) with very good internal consistency and test-retest reliability. All questions are scored on a Likert scale ranging from 0 to 4 and reflects the degree of distress in the last week. Total scores range from 0 to 212. It covers nine primary symptom dimensions. On all scales, higher scores indicate higher levels of complaints [52].

*Alcohol Use Disorder Identification Test (AUDIT):* The AUDIT is a World Health Organization (WHO) initiated screening instrument for problematic alcohol use in the past year. It consists of 10 statements about the amount of drinking and problems due to drinking. Items are scores on a Likert scale ranging from 0 to 4, therefore total scores range from 0 to 40, with higher scores indicating higher levels of excessive drinking. The self-reported AUDIT is used in this study [53].

*Drug Use Disorders Identification Test (DUDIT):* The DUDIT is a sensitive and specific instrument to screen for drug-related problems. It consists of 11 items and is developed as a parallel instrument to the AUDIT. Total scores range from 0 to 44, with higher scores indicate more drug use and problems related to drug use [54].

The AUDIT and the DUDIT are originally based on alcohol and drug use during the last year. In this study, at T1, T2 and T3 patients are asked about their alcohol or drug use in the previous 3 months instead of the previous year.

*MATE-Q-NL, module 1:* The Meten van Addicties voor Triage en Evaluatie (MATE-Q-NL, module 1), is a Dutch questionnaire that measures lifetime substance use and substance use over the past 30 days [55]. Only use over the past 30 days will be used as a secondary outcome measure in this study. When people are already abstinent at the first measurement assessment, substance use over the last month of their use will be administered, to prevent a flattering effect of the baseline measurement.

*Inventory of Interpersonal Problems (IIP-32):* The IIP-32 is a short version of the Inventory of Interpersonal Problems (IIP) and consists of two sections respectively asking participants what they find hard to do (for example ‘join in groups’) and things they do too much (for example ‘get irritated’) [56]. The IIP-32 consists of 32 items scored on eight subscales, with items scored on a Likert scale ranging from 0 to 4, with higher scores indicating higher levels of interpersonal problems. Internal consistency of the Dutch translation is acceptable [57].

*Difficulties in Emotion Regulation Scale (DERS):* The DERS measures emotion dysregulation across various dimensions on a 36-item self-report scale, with all questions scored on a Likert scale from 1 to 5. Higher scores indicate higher levels of emotion regulation problems. Internal consistency of the DERS is high and test-retest reliability is good [58].

*Trauma Related Guilt Inventory (TRGI):* The TRGI is a 32-item questionnaire with a 5-point Likert scale, measuring feelings of guilt related to trauma exposure. Higher scores indicate higher levels of guilt The TRGI has high internal consistency and adequate temporal stability [59]. In this study the same index will be used as in the study of Boterhoven [60]. Beliefs of victims of their role in trauma are part of the DSM-5 diagnosis (criterium D) and also an important focus in therapy (PE as well as EMDR and ImRs).

*Trauma Related Shame Inventory (TRSI):* The TRSI consists of 24 items, which can be scored on a 4-point Likert scale. Higher scores indicate higher levels of shame. In this study the same index will be used as in the study of Boterhoven [60]. As well as guilt, also shame is included as a symptom in the DSM-5. According the TRSI shame is described as a negative and painful self-evaluation in the traumatic context and a tendency to hide and withdraw from others. The TRSI had good generalizability and also good distinction between shame and guilt and can be used in both clinical research and practice [61].

*Self Expression and Control Scale (SECS):* The Zelf Expressie en Controle Vragenlijst (ZECV) is the Dutch translation of the Self Expression and Control Scale (SECS). This 40-item scale assesses internalised and externalised anger and anger control, scored on a Likert scale ranging from 1 to 4. Higher scores indicate higher levels of anger. Psychometric properties are good [62].

*Extension of the Life Event Checklist for DMS-5 (LEC-5):* The original LEC is a self-report questionnaire measuring exposure to possibly traumatic events. It was developed together with the CAPS-5 [63].

The LEC-5 is based on the DSM-5 and assesses exposure to 17 potentially traumatic events. According to the DSM-5, an event is considered traumatic if there is actual or threatened death, serious injury or sexual violence [64]. In the current study, several items have been added to the original LEC-5 to assess whether participants have experienced (recent) victimization and/or (recent) perpetration. Only recent victimization and recent perpetration will be used as a secondary outcome measure, the questions regarding lifetime trauma experiences will be used as a baseline assessment to identify the nature and extent of trauma experiences.

*PTSD Checklist for DSM-5 (PCL-5):* The PCL-5 is a 20-item self-report measure of PTSD symptoms according to the DSM-5 with a Likert scale ranging from 0 to 4. The total score is an index of PTSD symptom severity and has strong internal consistency and test-retest reliability [65]. This questionnaire will be assessed at the start of each therapy session to evaluate changes in PTSD symptoms during treatment.

*Session checklist:* A session checklist is used to gather retrospective information on the use of 12 categories of substances, on gambling, and the use of psychiatric medication in the days prior to the session. This information is registered at the start of each treatment session. This information will be used to keep up with modifications in substance and medication use during therapy.

